### 2.1. TEERMISO Study Patient Entry Criteria

#### 2.1.1. Describing Patient Groups

The clinical trial will include patients presenting with moderate to severe ischemic mitral regurgitation who may or may not require concomitant coronary artery bypass surgery (CABG) or percutaneous coronary intervention (PCI). Furthermore, patients will have undergone either S-SVRp or TMVp using TEER. Patients of any gender, race, or ethnicity will be eligible for inclusion in this study.

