The presence of elevated cardiac biomarkers (preferentially troponin) with a minimum value exceeding the 99th percentile of the upper reference limit (URL), accompanied by evidence of myocardial ischemia through the demonstration of at least one of the following:○New electrocardiogram (ECG) changes indicative of a new episode of ischemia, such as new ST-T changes or new left bundle branch block (LBBB), may be observed.○Ischemia signs.○An ECG examination has revealed the presence of pathological Q waves.○New evidence of loss of viable myocardium or new regional wall motion abnormalities should be sought.•Peri-CABG myocardial infarction.

In subjects presenting with normal baseline troponin values prior to CABG, elevations in cardiac biomarkers above the 99th percentile URL are indicative of peri-procedural myocardial necrosis. It is customary to consider biomarker elevation exceeding five times the 99th percentile URL, in conjunction with the emergence of new Q waves or a newly diagnosed left bundle branch block (LBBB), the formation of a new graft or native coronary artery occlusion as evidenced by angiography, or imaging findings suggestive of new loss of viable myocardium, as indicative of a CABG-related myocardial infarction.

Peri-percutaneous intervention (PCI) myocardial infarction.

For patients who have been treated with PCI and have normal baseline troponin values, any rises in cardiac biomarkers above the 99th percentile upper reference limit indicate the occurrence of peri-procedural myocardial necrosis. It has been standard practice to define PCI-related MI based on the observation of biomarker elevations greater than threefold the 99th percentile upper reference level. Furthermore, there is a recognized correlation between this subgroup and documented instances of stent thrombosis. A death that is sudden and unexpected, in the absence of any apparent cause, is classified as sudden cardiac death. This can be linked to cardiac arrest and may be followed by symptoms that indicate myocardial ischemia. In cases where this occurs, the death may be triggered by the onset of new ST elevation or new LBBB, as well as the presence of fresh thrombus, as identified by coronary angiography and/or autopsy. In the event of a death occurring before the scheduled blood sample collection or the anticipated appearance of cardiac biomarkers in the blood, the cause of death is deemed to be myocardial infarction.

Cardiac arrhythmias.

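### The general MI definition accepts pathological Q waves that are merely present, whereas the neighbouring ECG and imaging items and the peri-CABG rule require new findings

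*Protocol article*

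**What the plan says.** All the MI definitions stand in the protocol article, section 2.3, under Specific Adverse Event Definitions.

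- **General rule.** A biomarker above the 99th percentile upper reference limit, "accompanied by evidence of myocardial ischemia through the demonstration of at least one of the following". Four signs are listed:
  - "New electrocardiogram (ECG) changes indicative of a new episode of ischemia"
  - signs of ischemia, not specified further
  - "An ECG examination has revealed the presence of pathological Q waves"
  - "New evidence of loss of viable myocardium or new regional wall motion abnormalities should be sought"
- **Peri-CABG rule.** A biomarker above five times the limit "in conjunction with the emergence of new Q waves or a newly diagnosed left bundle branch block", or a new graft or native-vessel occlusion on angiography, or imaging that suggests new loss of viable myocardium.
- **Peri-PCI rule.** The text says it has been standard to "define PCI-related MI based on the observation of biomarker elevations greater than threefold the 99th percentile upper reference level". No ECG item is attached.

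The sentence that opens the MI definition says that at least one of the criteria is enough. Nothing says that the peri-procedural rules replace the general one.

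Section 2.1.1 describes "patients presenting with moderate to severe ischemic mitral regurgitation". Section 2.1.2 admits ischemic and non-ischemic disease as well as atrial functional regurgitation. Prior infarction is not an exclusion in section 2.1.3 or in Table 4.

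**The concern.** An MI safety endpoint should count infarcts that occur during or after the procedure. A pathological Q wave can be left over from an infarct years earlier. If its mere presence counts as the second element of the definition, the only new element needed is a biomarker above the 99th percentile. Two patients with the same procedural biomarker rise and no new ischemic sign would then be classified differently because one had an infarct in the past.

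The registry is one where this can happen. It enrols ischemic secondary mitral regurgitation, and section 2.3 describes subvalvular repair as treating papillary muscles moved by scar after infarction. The adverse-event text in section 2.3 also commits to comparing serious adverse events between the two groups and to giving each event type's incidence with a 95% confidence interval. To the extent that the rule picks up old infarcts, the MI line of that comparison would partly reflect infarct history instead of procedural injury.

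**Working it through.** The document gives no MI rate, sample size or power for this event, so there is no stated figure to reproduce. The check is textual.

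**1. The Q-wave sign beside its neighbours**

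| Rule | Item | Must it be new? |
|---|---|---|
| General | ECG changes (ST-T, left bundle branch block) | Yes |
| General | Signs of ischemia | Not stated, not specified |
| General | Pathological Q waves | **No** |
| General | Loss of viable myocardium or wall motion abnormality | Yes |
| Peri-CABG | Q waves | Yes |

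The same sign must be new in the peri-CABG rule and need only be present in the general rule.

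**2. The general rule applied as written.** Take a patient with unchanged Q waves from an infarct years ago, no new ECG change, no new imaging finding and no sign of ischemia. After the procedure the troponin is just above the 99th percentile.

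- Biomarker condition: met.
- At least one listed sign: met by the old Q waves.
- Result: MI.

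The same patient without the old Q waves meets no listed sign. Result: not MI.

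**3. Which patients are exposed**

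- *TEER without PCI, or mitral surgery without CABG.* Only the general rule applies, so step 2 holds directly. Section 2.3 plans a cohort without revascularization.
- *Surgery with CABG.* Old Q waves do not meet the peri-CABG rule. They still meet the general rule if the two operate side by side, which the text allows.
- *TEER with PCI.* The peri-PCI rule has no Q-wave item. The general rule again adds the old-Q-wave route if both operate.

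**4. Whether other text blocks the result.** The adverse-event paragraph in section 2.3 says that a pre-existing state counts as an adverse event only if it changes discernibly in nature, severity or degree. That sentence is general, does not mention ECG findings and is not repeated in the MI definition. The troponin rise could itself be read as the change, so the sentence leaves room for either classification.

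**5. Where the effect can reach.** The primary endpoint is LVEDVI at 10 years (section 2.2.1) and the main secondary endpoint is all-cause mortality (section 2.2.2). MACE consists of death, stroke, mitral re-intervention, worsening heart failure and heart-failure hospitalization. MI is in none of these.

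**6. Size.** If the general rule applied to everyone, the share meeting it on old Q waves alone would be at most (ischemic share) × (share of these with baseline Q waves) × (share with a biomarker above the limit). None of the three is given for this registry. Table 2 gives ischemic shares of 62.5% to 100%, but for other trials.

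**The case against.** The strongest reply is that the line should not be read alone. The stem asks for evidence of myocardial ischemia, and Q waves unchanged for years are not evidence of current ischemia. The adverse-event paragraph excludes unchanged pre-existing states, and serious and protocol-defined events are adjudicated at each center. The list is loosely worded throughout and cites an outside source for the definition, so the missing word may be an editing slip.

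Part of this stands. A careful adjudicator could refuse to count an old Q wave, so it would be too strong to infer that such patients certainly will be counted as new MIs. The document shows that the rule permits the count, not that it will be made. The defect remains, because the list itself names the presence of Q waves as sufficient evidence. Local adjudication without a written restriction also leaves five centers free to decide differently.

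A second reply is that the peri-CABG and peri-PCI rules naturally govern procedural biomarker rises in those patients. That is a reasonable reading, but no precedence is stated, and it leaves patients without revascularization exposed. Under it, CABG patients would need five times the limit plus a new finding, while a TEER patient without PCI would need only one times the limit plus an old Q wave.

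A third reply is that section 3 plans propensity weighting with a doubly robust analysis. This may balance etiology between the groups if etiology is in the model. It does not remove misclassified events, and the text does not say that safety incidences are weighted.

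**Conclusion.** The general MI definition is internally inconsistent on Q waves. Read literally, it can classify an old infarct plus a biomarker rise as a new MI. The consequence is limited to the MI safety incidence and its comparison between groups; the primary endpoint, mortality and MACE are untouched.

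A reader might want to put a number on it. Baseline Q waves in 20% to 50% of ischemic patients and biomarker exceedance in 80% to 100% would give 0.625 × 0.20 × 0.80 = 10% up to 1.0 × 0.50 × 1.0 = 50% of patients. Arms that are 80% and 60% ischemic with 30% Q waves would give 0.8 × 0.3 = 24% against 0.6 × 0.3 = 18%, a 6-point gap. The document does not support either result:

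- The Q-wave and exceedance shares and the split between arms are assumptions without a source in it. The ischemic range comes from other trials, whereas this registry also admits non-ischemic and atrial functional disease.
- The 6-point example sets exceedance to 100% in both arms. At 80% it would be 19.2% against 14.4%, or 4.8 points.
- Both calculations apply the general rule to everyone and ignore the separate CABG and PCI rules. The gap also ignores the planned weighting.

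Neither the size nor the direction of a difference between groups is therefore established. The conclusion rests only on the printed wording, the absence of a precedence rule, and eligibility criteria that admit patients with prior infarction.

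**What to change.** Reconcile the Q-wave item of the general MI definition in section 2.3 with the items around it and with the peri-CABG rule. It should require new pathological Q waves compared with the available pre-procedure ECG.

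The change costs one phrase in the definition. Events without a baseline ECG for comparison could not be classified on this item, although the other listed signs would remain open to them. The document does not say how often a pre-procedure ECG is on file, so that loss cannot be sized. Any MI already classified on the Q-wave item alone would need to be checked again against the baseline tracing.

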An adverse event (AE), as defined by the International Council for Harmonisation of Technical Requirements for Pharmaceuticals for Human Use (ICH), is any event that occurs during a clinical trial and that results in any of the following: a change in the condition of the study participant; a change in the participant’s status; or a new disease or syndrome that the participant develops. An adverse event must be considered clinically significant. Furthermore, it must occur in a participant who is taking part in the trial, regardless of whether the event is related to the study intervention. A pre-existing pathological state will only be designated as an adverse event if there is a discernible alteration in its character, severity, or degree.

A comparison will be made between the two groups with respect to the occurrence of any adverse effects that are deemed to be significant throughout the period of the experimental trial. The onus for adjudicating all serious and protocol-defined adverse events (AEs) will be borne by the clinical control specialists responsible for overseeing this study at each research center. Adverse events will be documented in accordance with specified safety endpoints. The report will provide detailed information on the incidence and prevalence of serious adverse effects, including the frequency of each adverse occurrence, the incidence rate per patient per annum, and the temporal distribution of adverse events. Moreover, the incidence of patients presenting with each discrete category of serious adverse event will be recorded. Safety metrics will be gathered throughout the duration of the patient follow-up period. Subsequently, the incidence of each event type will be calculated with 95% confidence intervals in alignment with the specified safety endpoints.

○Serious adverse event.

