It is requisite that each neurological event be allocated to a subcategory as follows:A transient ischemic attack can be defined as an abrupt episode of neurological deficit that is fully reversible within a 24 h period and does not demonstrate evidence of infarction on imaging studies.A cerebrovascular accident, or CVA, is a medical term used to describe either an ischemic or hemorrhagic stroke. Ischemic stroke is defined as a condition with a duration of more than 24 h, while hemorrhagic stroke is characterized by the occurrence of infarction on imaging. In the event of hemorrhagic conversion following an ischemic stroke, the classification remains consistent.Toxic metabolic encephalopathy (TME) is a condition characterized by impaired brain function resulting from disrupted systemic metabolism or exposure to external agents. It presents with altered levels of consciousness and awareness, as well as a lack of focal neurological signs and a negative brain scan.Other.Renal events.

The assessment of renal function will be categorized in accordance with the predicted glomerular filtration rate (eGFR), which will be determined through the application of both the Chronic Kidney Disease Epidemiology Collaboration (CKD-EPI) equation [39] and the European Kidney Function Consortium (EKFC) equation [40]. The extent of renal failure will be classified into different stages, as detailed in Table 6.

Two distinct categories of kidney-related events will be identified and defined:○Renal dysfunction.

Abnormalities in kidney function will be characterized by a rise in serum creatinine (Cr), exceeding 100% from the established baseline, and a Cr concentration exceeding 2.0.

○Renal failure.

A new criterion has been established for the initiation of hemodialysis in patients with renal dysfunction. It should be noted that the aforementioned definition excludes aquapheresis procedures that are solely intended for the removal of excess fluid volume.

Hepatic dysfunction.

Hepatic dysfunction is diagnosed when any two liver tests (total bilirubin, aspartate aminotransferase/AST, and alanine aminotransferase/ALT) exceed the upper normal limit by threefold. It is also diagnosed as the primary cause of death if liver dysfunction is identified.

Respiratory insufficiency.

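### The early-death rule for myocardial infarction states neither its scope nor an ischemia condition, and the hepatic rule makes liver dysfunction the primary cause of death whenever it is found

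*Protocol article*

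**What the plan says.** All the wording at issue is in Section 2.3 of the protocol article, among the specific adverse event definitions.

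- **General MI definition.** A raised cardiac biomarker must be "accompanied by evidence of myocardial ischemia through the demonstration of at least one of the following"; a list of ECG, clinical and imaging signs follows.
- **Peri-PCI MI, sudden death.** After the biomarker threshold for PCI patients, the paragraph turns to deaths: "A death that is sudden and unexpected, in the absence of any apparent cause, is classified as sudden cardiac death". It adds that ischemic symptoms may be present and that "the death may be triggered by the onset of new ST elevation or new LBBB, as well as the presence of fresh thrombus".
- **Peri-PCI MI, closing sentence.** For a death before the scheduled blood sample or "the anticipated appearance of cardiac biomarkers in the blood, the cause of death is deemed to be myocardial infarction".
- **Hepatic dysfunction.** The laboratory criterion is any two of bilirubin, AST and ALT above three times the upper limit. The next sentence reads: "It is also diagnosed as the primary cause of death if liver dysfunction is identified".
- **Use of the definitions.** Section 2.2.2 lists the incidence of serious adverse events as a secondary safety endpoint. The adverse events text in Section 2.3 states: "A comparison will be made between the two groups with respect to the occurrence of any adverse effects". It also promises an incidence with a 95% confidence interval for each event type, and gives adjudication of serious and protocol-defined events to specialists at each center.

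**The concern.** A safety comparison of open surgery with a transcatheter procedure needs event categories that mean the same in both arms. The closing sentence of the peri-PCI paragraph assigns a cause of death because a measurement is absent; it asks for no positive evidence. The hepatic sentence assigns a cause of death because an abnormality is present, without asking whether that abnormality led to the death. Centers that follow the text could record a fatal MI with no sign of ischemia, or a hepatic death in a patient whose liver tests rose as a consequence of something else. Centers that read the sentences differently would classify the same death differently. What is at stake is the MI incidence, the hepatic event profile and any breakdown of deaths by cause.

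**Working it through.** No arithmetic applies: the article states no number of early deaths, MIs or hepatic events. The check is to set the definitions side by side and run hypothetical deaths through them.

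**Step 1. Is ischemia a condition of the early-death rule?** The general definition asks for a biomarker rise and at least one sign of ischemia. A patient who dies before sampling cannot meet the biomarker part, so some substitute rule is reasonable. The ischemia part could still be met from symptoms, ECG, angiography or autopsy. The closing sentence does not ask for any of these. The sentences before it mention them, but only in permissive terms (they may be present), and nothing ties them to the closing sentence. The conflict with the general definition is therefore over ischemia, not over the missing biomarker.

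**Step 2. Which label applies?**

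| Hypothetical death | Sudden-death sentence | Closing sentence, taken literally | Result |
|---|---|---|---|
| PCI patient, sudden, unexplained, no sample, no ischemic sign | Sudden cardiac death | MI | Two labels, no rule of precedence |
| PCI patient, no sample, ischemic symptoms with new ST elevation or fresh thrombus | Ischemic findings present | MI | MI on any reading |
| CABG patient, sudden, unexplained, no sample | Applies only if the wording reaches beyond PCI | MI only if the wording reaches beyond PCI | Depends on unstated scope |
| Any patient, recognized non-cardiac cause, no sample | Does not apply, since a cause is apparent | MI only if the sentence stands alone | Depends on unstated scope |

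Only the second row has a settled answer.

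**Step 3. Does scope matter between the arms?** The peri-CABG definition has no rule for deaths before sampling. Section 2.3 attaches CABG to the surgical techniques and puts patients revascularized by PCI or CABG in one cohort. If the heading governs, the rule applies only to PCI patients, which by inference means mainly TEER patients; the article does not give the split. If the sentence is general, the rule adds MIs to whichever arm has more deaths before sampling. The direction of any distortion thus depends on a scope that is not written down.

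**Step 4. The hepatic rule.** The trigger is a test level. Read literally, once the laboratory criterion is met in a patient who dies, hepatic dysfunction is the primary cause of death. No causal judgment is requested, and no precedence is given if another cause is also recorded.

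**Step 5. Which results can move?** The primary endpoint is an echocardiographic volume index. The main secondary endpoint is death from any cause. MACE comprises death, stroke, mitral re-intervention, worsening heart failure and CHF hospitalization, so it counts every death and does not include MI. None of these depends on the two rules. What can move is the MI and hepatic counts in the safety tables and any cause-of-death breakdown.

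**The case against.** The strongest reply is that the closing sentence should be read in context. It ends a run of sentences about sudden, unexplained death with possible ischemic findings, and it sits under the peri-PCI heading. On that reading it covers only suspected coronary deaths in PCI patients for whom no biomarker could be obtained. The hepatic sentence may likewise be a garbled way of saying that hepatic dysfunction is also recorded when it is the cause of death. Serious and protocol-defined events are adjudicated at each center, and no endpoint above the safety tables uses MI or cause of death.

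Much of this stands, and it rules out several stronger readings that a reader might infer:

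- **Every death before sampling, including recognized hemorrhage, tamponade or stroke, becomes an MI.** This requires taking one sentence out of its paragraph. The defect is an unstated scope and condition, not a clear rule for all early deaths.
- **Laboratory timing fixes causes of death and MI counts in general.** Timing matters only for deaths before sampling. Other MIs rest on biomarker levels, with supporting evidence in the general and peri-CABG definitions, and the hepatic rule turns on a test level.
- **Bleeding and tamponade events vanish from their own categories.** They have separate criteria in Section 2.3, and nothing limits a patient to one event type. Only the attributed cause of death could change.
- **Surgical MI is inflated by a stated percentage.** That would need assumed rates applied to all 384 surgical patients, although the rule sits under a PCI heading.
- **The biomarker sampling schedule is missing.** A condensed article may leave that to the full protocol.

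What does not stand is the appeal to adjudication. The adjudicators work center by center and apply these same definitions, and a rule that deems the cause leaves them little room for judgment. The contextual reading is plausible, but the text does not state it.

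**Conclusion.** The concern holds in a limited form. The closing sentence under peri-PCI MI does not state its scope or require ischemia. It conflicts with the general MI definition and gives a sudden, unexplained death before sampling a second label. The hepatic sentence, as worded, turns a finding into a primary cause of death. Followed literally, both can misassign events in a between-group safety comparison to which the protocol commits itself.

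The effect on the primary endpoint, all-cause mortality and MACE is nil. The effect on the MI and hepatic tables cannot be sized from the documents, and its direction is open. The conclusion assumes that centers classify events by the published wording; if they all apply the contextual reading, little misassignment follows. The point should be corrected because the remedy is cheap, not because a large distortion has been shown.

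**What to change.** 1. State which patients and which deaths the closing sentence of the peri-PCI paragraph covers, and apply the same rule in both arms.
2. For a fatal MI without biomarkers, require the ischemic evidence that the paragraph already lists: symptoms with new ST elevation or new LBBB, or fresh thrombus at angiography or autopsy. Otherwise record the adjudicated cause, or undetermined.
3. Reconcile this rule with the sudden cardiac death label, so that one death receives one label or the order of precedence is explicit.
4. Reword the hepatic definition: an adverse event when the laboratory criterion is met, and a cause of death only when adjudicated as such.

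The cost is a few reworded sentences. The kinds of evidence are already named in the article and the adjudicators are already in place. The downside is that a few deaths will be recorded as undetermined.
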